#### Secondary Analyses

Between-groups differences at 8 weeks will be examined for the following continuous outcomes: IBD symptom perception (IBDSS); psychological processes (SCS, CompACT); chronic illness-related shame (CISS); work and social adjustment (WSAS); quality of life (EUROHIS-QOL-8, UK-IBDQ), and disease activity (Mayo Score for ulcerative colitis participants; and Harvey-Bradshaw Score for Crohn's Disease participants). All analyses are to be conducted using ANCOVA with baseline values as a covariate.

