### Primary and Secondary Outcomes in the RCT

Participants completed self-report measures at four different times: baseline (T0), follow-up (T1), and 3-month (T2), and 12-month (T3) follow-ups (Table 2). Participants additionally provided blood and stool samples at T0 and T3. Mayo Scores or Harvey-Bradshaw Scores were assessed at T0 and T2.

**Table 2 T2:** Schedule of enrollment, intervention, and assessments.

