### Data Analysis

All analyses are planned as intent-to-treat (ITT). The primary outcome will be the psychological distress (DASS-21–*depression, anxiety, and stress*) measured at 8 weeks (immediately post-intervention) between the two intervention groups and adjusting for baseline scores using ANCOVA. We will examine the ANCOVA's assumptions through standard tests and residual plots and perform transformations. The magnitude of the differences between-treatment groups will be expressed as the standardized mean difference.

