#### Longitudinal Outcomes

We will use Mixed Models of Repeated Measures (MMRM) to examine for Group^*^Time interaction effects on each of the continuous outcomes from baseline, 9 weeks, 3 and 12 months; the DASS-21, the IBD symptom perception scale; SCS, CompACT, CISS, WSAS, EUROHIS-QOL-8, UK-IBDQ, and Mayo or Harvey-Bradshaw score.

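### Disease activity is to be compared at 8 weeks, but the Mayo and Harvey-Bradshaw scores are scheduled only at baseline and 3 months, so that ANCOVA has no outcome data and only the 3-month part of the mixed model can be estimated

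*Protocol article*

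**What the plan says.** **Schedule.** Primary and Secondary Outcomes in the RCT defines the assessment points as "baseline (T0), follow-up (T1), and 3-month (T2), and 12-month (T3) follow-ups". It then states that "Mayo Scores or Harvey-Bradshaw Scores were assessed at T0 and T2". In Table 2 the Mayo and Harvey-Bradshaw rows are each marked under t0 and t2 only.

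**Analysis.** Data Analysis places the primary comparison at the end of treatment, "measured at 8 weeks (immediately post-intervention"; this is the T1 visit. Secondary Analyses keeps the same time point ("Between-groups differences at 8 weeks will be examined for the following continuous outcomes") and its list ends with "disease activity (Mayo Score for ulcerative colitis participants; and Harvey-Bradshaw Score for Crohn's Disease participants". All of these comparisons are to be ANCOVAs with the baseline value as covariate. Longitudinal Outcomes plans mixed models for repeated measures with a group-by-time interaction for "each of the continuous outcomes from baseline, 9 weeks, 3 and 12 months", and its list ends with "UK-IBDQ, and Mayo or Harvey-Bradshaw score". Exploratory Outcomes adds reliable change indices from baseline to 9 weeks for every outcome.

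**The concern.** The analysis text sets a time point at which the schedule yields no disease-activity score. This is not a detail left to a fuller document: the article states both the visits and the analysis time point, and they cannot both hold for this outcome.

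Disease activity is one of the superiority aims listed under Aims of this Study. It is also the only outcome for which the article says the assessor was blinded to allocation (Disease activity section). The Discussion concedes that control participants knew they had not been given the intervention and that this may colour their questionnaire answers, so an outcome with a blinded clinical component carries particular weight. If its stated time point has no data, whoever runs the analysis must pick another time point or model, possibly after seeing the results.

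**Working it through.** The article gives no numerical figure for disease activity to reproduce. The check sets the schedule against each planned analysis and then asks which contrasts can be estimated.

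**1. Visits available and visits needed**

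| Planned analysis | Visits needed | Visits with Mayo or Harvey-Bradshaw | Result |
|---|---|---|---|
| ANCOVA at 8 weeks (Secondary Analyses) | T0, T1 | T0 | No outcome value; cannot be run |
| Mixed model (Longitudinal Outcomes) | T0, T1, T2, T3 | T0, T2 | 2 of 4 visits; 1 of 3 post-baseline visits |
| Reliable change, baseline to 9 weeks (Exploratory Outcomes) | T0, T1 | T0 | Cannot be computed |

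The article labels the post-intervention visit 8 weeks in some places and 9 weeks in others. That is a separate inconsistency and does not matter here: under either label the visit is T1, and neither score is scheduled at T1.

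**2. How the mismatch is confined**

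The 8-week list covers nine instruments: the IBD symptoms scale, SCS, CompACT, CISS, WSAS, EUROHIS-QOL-8, IBDQ-UK, partial Mayo and Harvey-Bradshaw. In Table 2 the first seven are marked at t1 and the last two are not. A time point that suits the questionnaires has been applied to two clinical indices with a different schedule.

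**3. What the mixed model can still estimate**

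Let g be 0 for TAU and 1 for LIFEwithIBD + TAU. The mean model with four visits is

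E(Y) = b0 + bG·g + b1·[T1] + b2·[T2] + b3·[T3] + c1·g·[T1] + c2·g·[T2] + c3·g·[T3],

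which has 8 parameters. The group-by-time contrasts are c1 (9 weeks), c2 (3 months) and c3 (12 months).

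With all four visits there are 2 × 4 = 8 cell means, the design has rank 8, and all three contrasts are estimable. With T0 and T2 only there are 2 × 2 = 4 cell means and the rank is 4 of 8:

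- c1 and c3 enter none of the four observed cell means, so they are not estimable.
- c2 = (mean at T2 − mean at T0 in the intervention arm) − (mean at T2 − mean at T0 in the control arm), so it is estimable.

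A numerical check of the design matrix gave the same result: rank 4, with c2 estimable and c1 and c3 not.

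**4. Primary outcome**

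Table 2 marks DASS-21 at t0, t1, t2 and t3. The primary ANCOVA, and the sample size of 58 derived for it, do not depend on any of this.

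**The case against.** The strongest reply is that a between-group analysis of disease activity survives. Longitudinal Outcomes names baseline and 3 months among its time points, exactly the two visits at which the scores exist, and the 3-month contrast can be estimated. A reader might infer from the mismatch that neither planned analysis can be run, or that disease activity has no between-arm comparison at all. The article does not support that: a two-visit model fits. What remains is that the ANCOVA is impossible as stated, that two of the three mixed-model contrasts have no data, and that nowhere does the article say the 3-month contrast is the one intended.

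A reader might also infer that the multiple imputation under Attrition, Protocol Non-adherence, and Missing Data would fill in T1 and T3 scores for everyone. That section deals with data lost through non-retention, withdrawal or skipped items. It does not propose imputing an assessment never scheduled for any participant, and the plan should not be charged with that. Equally, imputation offers no remedy here.

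A third tempting reading is that analysing ulcerative colitis and Crohn's disease separately is itself a fault in a small trial. The two indices have different components and each belongs to one disease, so separate analyses are coherent. The article does not give the split between the diseases, so no loss of precision can be calculated from it, and its sample size is claimed only for the primary analysis.

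Finally, this is one of many secondary outcomes. That is fair, and it bears on how serious the point is, not on whether it is right.

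**Conclusion.** The point holds in a limited form. For disease activity, the 8-week ANCOVA has no outcome data for any participant and cannot be run; the mixed model can deliver one of its three group-by-time contrasts, at 3 months; and the baseline-to-9-week reliable change indices cannot be computed. The conclusion rests only on the schedule, where text and Table 2 agree, and on 8 or 9 weeks meaning the T1 visit, as Data Analysis indicates by calling it immediately post-intervention. No assumption about effect size, variance or disease mix is needed.

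The primary outcome, its sample size and the questionnaire outcomes on the 8-week list are untouched. This should be corrected, but it is an error in a secondary outcome and does not threaten the trial's main inference.

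**What to change.** - **Secondary Analyses:** remove disease activity from the 8-week list. State its between-group analysis as ANCOVA of the T2 (3-month) score with the T0 score as covariate, run separately for the partial Mayo score in ulcerative colitis and the Harvey-Bradshaw score in Crohn's disease, as already planned.
- **Longitudinal Outcomes:** remove the two scores from the four-visit mixed model, or restrict them to T0 and T2. If they stay, say whether the ANCOVA or the two-visit model gives the reported 3-month result, since both address the same between-group difference.
- **Exploratory Outcomes:** limit the baseline-to-9-week reliable change indices to outcomes measured at T1. This also removes the blood and stool markers, which Table 2 schedules only at t0 and t3.

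The cost is wording; no new data are needed. Adding a T1 assessment is not an option, because the article reports the scores as already collected. The downside is that disease activity is reported at 3 months and not immediately after the intervention. The change should be made and dated before the disease-activity data are compared by arm.

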## Abstract

**Background:** There is ample evidence of the high mental health burden caused by Inflammatory Bowel Disease (IBD). Several constructs such as experiential avoidance, cognitive fusion, shame, and self-criticism have recently emerged as potential intervention targets to improve mental health in IBD. Psychotherapeutic models such as Acceptance and Commitment Therapy and compassion-based interventions are known to target these constructs. In this protocol, we aim to describe a two-arm Randomized Controlled Trial (RCT) testing the efficacy of an ACT and compassion-focused intervention named Living with Intention, Fullness, and Engagement with Inflammatory Bowel Disease (LIFEwithIBD) intervention + Treatment As Usual (TAU) vs. TAU in improving psychological distress, quality of life, work and social functioning, IBD symptom perception, illness-related shame, psychological flexibility, self-compassion, disease activity, inflammation biomarkers, and gut microbiota diversity.

**Methods:** This trial is registered at ClinicalTrials.gov (Identifier: NCT03840707, date assigned 13/02/2019). The LIFEwithIBD intervention is an adaptation to the IBD population of the Mind programme for people with cancer, an acceptance, mindfulness, and compassion-based intervention designed to be delivered in a group format. The LIFEwithIBD intervention's structure and topics are presented in this protocol. Participants were recruited at the Gastroenterology Service of the Coimbra University Hospital between June and September 2019. Of the 355 patients screened, 61 participants were selected, randomly assigned to one of two conditions [experimental group (LIFEwithIBD + TAU) or control group (TAU)] and completed the baseline assessment. Outcome measurement took place at baseline, post-intervention, 3- and 12-month follow-ups.

**Discussion:** Results from this RCT will support future studies testing the LIFEwithIBD intervention or other acceptance and/or compassion-based interventions for IBD.

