### Aims of this Study

This study aims to conduct a two-arm RCT to test the efficacy of a new integrative ACT and compassion-based intervention, the Living with Intention, Fullness, and Engagement with Inflammatory Bowel Disease (LIFEwithIBD) intervention, which was adapted from the Mind programme for people with cancer (52) to the IBD context. This intervention (LIFEwithIBD + TAU)'s superiority in improving psychological distress (primary outcome), quality of life, work and social functioning, IBD symptom perception, illness-related shame, psychological flexibility, self-compassion, disease activity, inflammation biomarkers, and gut microbiota diversity will be compared to TAU.

The contents of the LIFEwithIBD intervention and the design of the RCT are presented in this paper.

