#### Participant Selection

Inclusion criteria were: (a) 18 to 65 years old; (b) being able to read and write Portuguese; (c) having an IBD diagnosis for at least 6 months; (d) being able to give informed consent. Exclusion criteria were: (a) having started a new treatment for IBD in the previous 6 months (in the case of anti-TNF and immunosuppressive therapy) or 2 months (in the case of steroid or aminosalicylate therapy); (b) presenting a diagnosed psychiatric disorder (major depressive disorder, psychotic disorder, bipolar disorder, substance abuse), severe depression, or suicidal ideation (assessed by the Patient Health Questionnaire-9 [PHQ-9 (55)])^1^; (c) undergoing any other form of psychological intervention; (d) being pregnant. Patients non-eligible due to criteria (b) were referred to national mental healthcare services.

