### Sample Size

An *a priori* power analysis for this study was performed. In the absence of meta-analytic evidence, we have used data from Wynne et al. (25). Large reductions in mood symptoms were reported at follow-up for depression [*SMD* = 0.88 (0.557–1.21)], anxiety [*SMD* = 0.75 (0.423–1.068)], and stress [*SMD* = 1.1 (0.88–1.559)], even after adjustment for baseline values. Using the smallest of these effect estimates (anxiety), the inclusion of the baseline values as a covariate, an alpha of 0.05 and 80% power, we estimate that a total sample size of *n* = 58 would be required to power the primary analysis.

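### Disease activity is a single IBD-wide aim, but it is planned as Mayo in ulcerative colitis and Harvey-Bradshaw in Crohn's disease, with no combined estimate

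*Protocol article*

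**What the plan says.** Aims of this Study treats disease activity as one item in a list on which the intervention's superiority is to be tested: "illness-related shame, psychological flexibility, self-compassion, disease activity, inflammation biomarkers, and gut microbiota diversity will be compared to TAU". The population is IBD as a whole. The diagnostic entry criterion under Participant Selection is "having an IBD diagnosis for at least 6 months", with no restriction to one disease.

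The Disease activity section gives the partial Mayo score to participants with ulcerative colitis and the Harvey-Bradshaw score to those with Crohn's disease, and the components differ. Secondary Analyses carries this division into the ANCOVA list as "disease activity (Mayo Score for ulcerative colitis participants; and Harvey-Bradshaw Score for Crohn's Disease participants", with the baseline value as covariate. Longitudinal Outcomes names Mayo or Harvey-Bradshaw as one entry for the mixed model and does not say whether that means one model or two. No section gives a common scale, a pooled estimate or a rule for reading the two results together.

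On timing, Secondary Analyses sets the comparison at 8 weeks. Primary and Secondary Outcomes in the RCT, and Table 2, place both scores at T0 and T2 only.

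**The concern.** There is one question but two answers, each from a separate set of patients. If one score favours the intervention and the other does not, the article gives no way to state a conclusion on disease activity in IBD. If both are null, the intervals are so wide that little has been learned. The precision of the full sample is available but not used.

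The longitudinal model has the same difficulty. Read as two models, it repeats the split. Read as one model on raw scores, it mixes two instruments with different units, and the treatment effect has no clear meaning.

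**Working it through.** **Inputs.**
- Effect benchmark: "Using the smallest of these effect estimates (anxiety", which is "0.75 (0.423–1.068" with its interval. This is a mood effect. No effect for disease activity is given.
- Error rates: "an alpha of 0.05 and 80% power". Two-sided is assumed.
- Sample with baseline data: 61 (Abstract).
- Split between ulcerative colitis and Crohn's disease: not given. Assumed shares are 30% to 70%.
- Correlation between baseline and follow-up score: not given. Taken as 0 (unadjusted) and 0.5.

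**1. The plan's own figure.** A two-sample t-test at SMD 0.75, two-sided 0.05 and 80% power needs 28.9, so 29, per arm and 58 in total. This reproduces the stated 58, with no numerical gain taken for the baseline covariate. The same noncentral-t method is used below.

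**2. Power by size of the diagnosis group**, unadjusted, near-equal arms:

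| Patients analysed | Arms | SMD 0.5 | SMD 0.75 |
|---|---|---|---|
| 18 (about 30%) | 9 / 9 | 17% | 32% |
| 24 (about 40%) | 12 / 12 | 22% | 42% |
| 30 (about 50%) | 15 / 15 | 26% | 51% |
| 43 (about 70%) | 21 / 22 | 36% | 67% |
| 61 (all) | 30 / 31 | 48% | 82% |

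Whatever the true split, the smaller group cannot exceed 30 of 61. At least one of the two tests therefore has at most about 51% unadjusted power at SMD 0.75.

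**3. Baseline adjustment.** ANCOVA multiplies the residual SD by √(1 − r²). With r = 0.5, SMD 0.75 acts as 0.75 / √0.75 = 0.866. Power is then 63% for 15 versus 15 and 91% for all 61. Both rise and a gap remains.

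**4. What combining recovers.** With equal arms the variance of an SMD is roughly 4/n.
- 30 patients: SE = √(4/30) = 0.365, 95% half-width 1.96 × 0.365 = 0.72.
- 18 patients: SE = √(4/18) = 0.471, half-width 0.92.
- Inverse-variance combination of 18 and 43: 1 / (18/4 + 43/4) = 4/61, SE 0.256, half-width 0.50.

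The combined precision is that of all 61, whichever way the diagnoses divide.

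**5. Chance imbalance of arms within a diagnosis.** If 30 of the 61 had one diagnosis and 32 were in the experimental arm, the 95% range for that diagnosis in the experimental arm is 12 to 20. Power at SMD 0.75 falls from 51% (15 / 15) to 49% (12 / 18) or 46% (10 / 20), a loss of 2 to 5 points.

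These figures assume that all 61 give T2 scores. The Discussion names retention as the greatest limitation, so they are upper values.

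**The case against.** The strongest reply is that this is a secondary outcome in a condensed article. The sample size is said only to be what "would be required to power the primary analysis", and that analysis concerns psychological distress. Low power on a secondary outcome is not a planning error. Two instruments are needed because the diseases are scored differently, and a combining rule could sit in a fuller analysis plan. All of this stands, and it is why the point is an improvement and not a fault in the design. It does not remove the point: the article states a disease-activity analysis by diagnosis, and that analysis does not match the single aim it serves.

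A reader might infer more than the documents support:
- **That neither test can answer the superiority question.** Each is a proper randomised comparison within its diagnosis. It is imprecise, not invalid.
- **That each test uses half the sample.** No split is reported, and an even one is only an assumption.
- **That the lack of described stratification by diagnosis is material.** Its likely cost is 2 to 5 power points. The loss comes from dividing the sample.
- **That two tests at 0.05 create a special false-positive problem.** For two independent tests, 1 − 0.95² = 9.75%. But Secondary Analyses lists several other measures, the article states no adjustment across them, and nothing says that either activity score alone would count as success. Any multiplicity issue is general to the secondary outcomes.

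**Conclusion.** The point holds as a mismatch between one stated aim and an analysis that yields two unconnected results. At the benchmark SMD of 0.75, each test has about 32% to 67% unadjusted power for diagnosis shares of 30% to 70%, against 82% for one analysis of all 61. The size rests on three assumptions: the split, a two-sided t-test approximation, and an anxiety effect borrowed as a yardstick. A smaller true effect on disease activity lowers every figure (at 0.5, 26% for an even split against 48% for all 61). The 8-week time point is a separate inconsistency with the assessment schedule. It matters here because any disease-activity analysis, split or combined, has post-baseline data only at T2.

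**What to change.** Add one combined disease-activity estimate and name it as the answer to the stated aim.

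1. Divide each score by its baseline SD within diagnosis, then fit one ANCOVA with treatment, standardised baseline score and diagnosis. Alternatively, combine the two diagnosis-specific SMDs by inverse variance. Either fits the standardised mean difference that Data Analysis already uses to express effects.
2. Report the separate Mayo and Harvey-Bradshaw results alongside.
3. Treat the Longitudinal Outcomes entry the same way, and state that raw scores from the two instruments are not mixed.
4. Run the analysis at T2, and reconcile the 8-week wording in Secondary Analyses with the assessment schedule and Table 2.

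The cost is a few lines of analysis-plan text and one extra model on scores that the schedule already collects. The downside is that the estimate is in SD units and averages over two diseases whose effects may differ. The separate results let readers check that.

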#### Longitudinal Outcomes

We will use Mixed Models of Repeated Measures (MMRM) to examine for Group^*^Time interaction effects on each of the continuous outcomes from baseline, 9 weeks, 3 and 12 months; the DASS-21, the IBD symptom perception scale; SCS, CompACT, CISS, WSAS, EUROHIS-QOL-8, UK-IBDQ, and Mayo or Harvey-Bradshaw score.

#### Exploratory Outcomes

Reliable change indices between baseline and 9 weeks will be calculated for all outcomes and correlated with demographics to examine for subgroup efficacy predictors. For exploratory analyses focused upon proportionate data, such as comparisons of mood dysfunction outcomes, McNemars' test can be used to examine within-group differences across time points.

#### Attrition, Protocol Non-adherence, and Missing Data

All participants recruited into the study, regardless of treatment group, are to have as much data as possible recorded as fully as possible in accordance with this protocol. Missing data will be monitored to avoid bias by attrition or patterns of missingness. All cases of missing data, including non-retention of participants or withdrawal of consent, are to be recorded by research staff. Where data is missing, the frequency and reasons for missing data are to be recorded. Missing data is to be examined to see if the missingness is informative to the study, for example, if specific variables are missed systematically by an identifiable participant pattern.

In situations where data is missing, the data collected up to that point will be used provided the participant has not withdrawn their consent or requested that the information be removed. If missing data is considered Missing Completely at Random or Missing at Random (MCAR or MAR), multiple imputation methods will be used to estimate missing values. The accepted minimum number of imputations is five to estimate the missing data from existing data. If data appears to be missing in a non-random way (Missing Not At Random, MNAR), then this data can be examined for potential biases or patterns statistically, and missing values can then be estimated using monotonic methods.

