## Discussion

Among those designed for or tested in IBD, the LIFEwithIBD intervention is the first to integrate ACT and compassion approaches. The RCT presented in this protocol paper will provide evidence on the efficacy of this intervention (which was delivered along with TAU) in improving health outcomes in comparison to the exclusive delivery of TAU (medical treatment). Due to the inactive nature of the control condition, future studies should compare the intervention's efficacy to other conditions such as active controls (e.g., psychoeducation) and other psychological interventions tested in IBD, such as Cognitive and Behavioral Therapy (86) or Hypnotherapy (87). The use of an inactive control will indeed be a significant limitation to this RCT, especially considering that participants allocated to this condition were aware of their non-allocation to the intervention group, which may influence answers to the administered self-report questionnaires. Also, contact with a group of people with the same pathology, as well as with the therapists, may in itself provide therapeutic effects only experienced by the experimental group, which adds to the disparity between the study groups. Nevertheless, considering this is the first time the LIFEwithIBD intervention will be tested, the use of an inactive control may provide useful preliminary results on the effects of the intervention.

The greatest limitation to this RCT appears to be participant retention, similarly to previous RCTs testing group interventions in this population, which also showed large attrition rates (25, 86). In the current study this may have been due to participants not being compensated for their participation besides receiving the intervention. Results from this RCT will act as support for future studies testing the LIFEwithIBD intervention or other acceptance and/or compassion-based interventions for IBD.

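### The rule for MNAR data names a method that, on its usual meaning, assumes MAR, so no stated analysis addresses outcome-dependent dropout

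*Protocol article*

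**What the plan says.** The section on attrition, protocol non-adherence and missing data in the protocol article sets a two-way rule.

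- For data considered MCAR or MAR, "multiple imputation methods will be used to estimate missing values". A floor is given: "The accepted minimum number of imputations is five".
- For data that appear MNAR, "this data can be examined for potential biases or patterns statistically", and then "missing values can then be estimated using monotonic methods". The last term is not defined anywhere in the article.

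The same section asks staff to collect as much data as possible on everyone, to record how often and why data are missing, and to check whether missingness is informative. Under Data Analysis, all analyses are intent-to-treat and the primary one is a baseline-adjusted ANCOVA of the DASS-21 after the intervention. Under Longitudinal Outcomes, an MMRM is fitted across all time points. The Discussion states: "The greatest limitation to this RCT appears to be participant retention".

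**The concern.** A plan that separates MAR from MNAR needs a method for the MNAR branch that actually relaxes MAR. The method named here does not, on any usual meaning of the term. It mistakes the shape of the missing data for the reason the data are missing.

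The practical risk is false reassurance. Suppose experimental-arm participants with missing post-intervention scores benefited less than the model predicts from those who stayed. Imputing them from observed participants then credits them with a benefit they did not have. Under the stated rule, that same optimistic figure could be reported as the analysis that allowed for MNAR.

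A second weakness is the trigger. The method depends on how the missingness appears, but MAR and MNAR differ only in how missingness relates to unobserved values. Recorded reasons can inform a judgement; the observed data alone cannot decide it.

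**Working it through.** **1. The plan's own figure.** The only planning number bearing on this is the effect size. The Sample Size section takes SMD 0.75 (anxiety), alpha 0.05 and 80% power, and arrives at 58 in total. Taking the test as two-sided (the article does not say), an exact t calculation with 29 per arm gives power 0.801, and an ANCOVA F-test with f = 0.75/2 = 0.375 and one covariate at N = 58 also gives 0.801. The figure of 58 reproduces, and nothing below changes it.

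**2. What each stated method assumes.**

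| Stated method | Assumption about missing values |
|---|---|
| Multiple imputation | MAR (as the plan itself says) |
| MMRM | MAR (likelihood-based) |
| ANCOVA | does not model dropout; relies on the imputation |
| Monotonic methods, for MNAR | usual meaning: models fitted to observed data, so MAR |

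The article names no delta adjustment, pattern-mixture model, selection model or reference-based imputation. That absence alone could be left to an analysis plan. The error is that the method which is named does not fit the mechanism it is assigned to.

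**3. Size of the possible bias (illustration).** Let d be the effect in participants with observed scores, p the share of experimental-arm post-intervention scores that are missing, and k the amount in SD by which those participants are truly worse than MAR predicts. Control-arm missing scores are taken to be MAR.

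- True effect over all randomised = (1 − p)·d + p·(d − k) = d − p·k
- MAR-type imputation returns d
- Overstatement = p·k

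The value d = 0.75 is the planning value. The values of p and k are assumptions, because the text gives no rate of missing post-intervention scores.

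| p | k = 0 | k = 0.25 | k = 0.50 | k = 0.75 |
|---|---|---|---|---|
| 0.20 | 0.00 | 0.05 | 0.10 | 0.15 |
| 0.40 | 0.00 | 0.10 | 0.20 | 0.30 |

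The last column is the case where those with missing scores do no better than control (k = d). The true effect is then 0.75 × 0.80 = 0.60 at 20% missing and 0.75 × 0.60 = 0.45 at 40%.

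**4. Check by simulation.** The post-intervention score was imputed by regression on baseline within arm, with an assumed baseline correlation of 0.6 and control-arm missingness at half the experimental-arm rate.

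| p | k | True effect | Imputed effect |
|---|---|---|---|
| 0.20 | 0 | 0.753 | 0.751 |
| 0.20 | 0.25 | 0.700 | 0.749 |
| 0.20 | 0.50 | 0.648 | 0.749 |
| 0.20 | 0.75 | 0.602 | 0.749 |
| 0.40 | 0.75 | 0.451 | 0.752 |

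The imputed effect stays near 0.75 whatever the shift, and the gap matches p·k.

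**The case against.** **The sentence is a permissive contingency in a condensed article.** It says what can be done, not what will be done, the term is undefined, and a fuller analysis plan may exist. This stands as far as it goes: the operative rule is multiple imputation, and missing detail on sensitivity analyses is not a fault here. It does not rescue the sentence, because a method is named for MNAR data and no usual meaning of that name makes it suitable.

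**The plan does protect against attrition.** A reader might infer that there is no valid protection at all. The documents do not support that. Multiple imputation and the MMRM handle MAR dropout, reasons for missingness are recorded, and data are sought on all participants. The gap is confined to outcome-dependent dropout.

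**The branch can be operated.** The plan proposes no formal test of MAR against MNAR, and a judgement from recorded reasons is possible, if fallible. So it is too strong to call the rule unworkable. The fair criticism is that whether an MNAR analysis is run should not hang on that judgement.

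**Outcome-driven dropout is not documented.** The reasons given are lack of time or transport before the intervention began and, as a possible explanation, the absence of compensation. Neither is lack of benefit. The losses visible in the text (76 randomised to 61 with baseline, 15/76 = 19.7%; 38 allocated to 32 in the experimental arm, 6/38 = 15.8%) fall before or at baseline and say nothing about missing post-intervention scores. Non-completers are defined by attendance, and nothing shows that they lack questionnaires. All of this stands, and it is why the bias figures are illustrative only.

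**Five imputations.** A reader might also infer that five is too few for this trial. The text sets five as a minimum, so any larger number complies, and without a rate of missing post-intervention scores the shortfall cannot be shown. No finding is made on that.

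**Conclusion.** The point holds in a limited form. The MNAR sentence confuses a missingness pattern with a mechanism and, on the usual meaning of its term, would yield a MAR estimate under an MNAR label. As a result, no stated method addresses outcome-dependent dropout in a trial whose authors regard retention as its main weakness.

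The possible overstatement is the missing share times the shift. It is zero if MAR is true, 0.05 to 0.10 SD at 20% missing with shifts of 0.25 to 0.5 SD, and 0.15 SD (20% missing) to 0.30 SD (40% missing) if those with missing scores gain nothing over control. The last pair is the unfavourable end of the assumed range, not an expectation. The figures assume an effect of 0.75 SD in those observed and MAR missingness in the control arm; informative dropout among controls would change the net bias.

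This should be fixed. It does not affect the sample size, and it does not undermine the main analysis if missingness is MAR.

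**What to change.** - Delete the sentence that assigns monotonic methods to MNAR data, and with it the choice of method according to how the missingness appears.
- Keep MAR-based multiple imputation as the main approach.
- Prespecify one MNAR sensitivity analysis of the post-intervention DASS-21 contrast, run whatever the missingness looks like. A delta-adjusted tipping-point analysis is suitable: worsen the imputed experimental-arm scores in fixed steps, for example from 0 to 0.75 SD, and report the step at which the conclusion changes. Control-based imputation of the experimental arm can be added if wanted.
- Fix the range of shifts before the outcome data are analysed.

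Raising the number of imputations is optional and already allowed by the stated minimum. Imputing separately by arm with many predictors is not required, and with about 30 per arm it could be unstable.

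The cost is a change of wording and a little programming, with no new data and no change to the 58. The sensitivity estimate will usually be less favourable to the intervention than the main one.
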